### Primary outcome parameter

Psychological distress in the past week, as indicated by the sum score of the Brief Symptom Inventory 53 item version (BSI-53), is the primary clinical outcome parameter. The BSI-53 is a self-report questionnaire and an abbreviated version of the Symptom Checklist-90 (SCL-90) [33, 42]. The BSI is validated for older adults and preferred over the SCL-90 since validation studies in older adults did not indicate any information loss compared to the SCL-90 [43]. We have chosen for psychological distress as the primary outcome parameter since 1) older patients with personality problems are rarely referred to geriatric mental healthcare for personality problems specifically, but nearly always for associated affective symptoms and 2) the study includes patients with a variety of personality disorders. Since the reliability of the Dutch BSI-53 subscales is rated as good and their convergent and divergent validity has been found to be satisfactory [42], subscale scores will be examined as secondary outcome parameters.

### Economic evaluation

The EuroQol-5D-5 L (EQ-5D-5 L), a generic self-report instrument, will be administered to measure health-related quality of life at the time of assessment [44]. It consists of five questions, each related to a specific dimension of health status: mobility, self-care, usual activity, pain/discomfort and anxiety/depression. The utility score of the EQ-5D-5 L will be used to calculate Quality-Adjusted Life-Years (QALYs) [45]. Medical consumption and other cost data will be collected by means of structured telephone interviews, as previously done in a younger patient group [44]. Since a considerable amount of resource use is situated outside (mental) healthcare institutions, data of formal registries such as hospital information systems or insurer’s databases are incomplete [44]. Therefore, patient-reported prospective cost diaries [46] or retrospective cost interviews [47], are the preferred instruments covering all relevant events. We have chosen a 3-month recall interview [48, 49] since a prospective cost diary or a recall interview over a longer period are expected to lead to more missing items.

### Secondary outcome parameters

A number of secondary outcome parameters have been chosen to specify the extent and nature of the effect of group schema focused therapy in later life.

#### Psychotropic drug use

Data on current psychotropic drug use and changes in between assessments will be collected as part of the telephone interviews, described above.

#### Life satisfaction

Life satisfaction will be assessed with Cantril’s ladder, a single self-report question to rate one’s current life situation on a scale (from 0 to 10) [50]. Life satisfaction is a conceptualization of subjective wellbeing which stresses the cognitive evaluation of one’s life situation, in contrast to for example feelings such as happiness. A score of 0 indicates ‘the worst possible life for you’ and 10 ‘the best possible life for you’.

#### Mental wellbeing

Mental wellbeing is assessed with the Warwick-Edinburgh Mental Well-being Scale (WEMWBS) [51]. Mental health and mental illness have been shown to be related but distinct concepts [52]. Reduction or absence of mental illness does not necessarily imply good mental health and wellbeing. The WEMWBS focusses on mental wellbeing and consists of 14 items covering positive affect, satisfying interpersonal relationships and positive functioning. Items have to be rated on a 5-point Likert scales assessing the frequency of the positive feeling over the past 2 weeks. A higher sum score indicates a better mental wellbeing.

#### Personality functioning

Personality functioning is assessed with the Severity Indices of Personality Problems – Short Form (SIPP-SF) [53]. The SIPP-SF assesses five core domains of (mal)adaptive personality functioning defined in the DSM-5 alternative dimensional personality disorders model, namely: Identity Integration, Self-Control, Relational Functioning, Social Concordance and Responsibility. The 60-items of the questionnaire consists of propositions referring to the last three-months, which are answered on four-point Likert scales, ranging from fully agree to fully disagree. Higher scores imply more adaptive functioning. The SIPP-SF has been studied in an older sample and was suggested to be a useful clinical tool to assess effects of therapy on levels of personality functioning in this age group [54].

#### Interoceptive body awareness

Interoceptive body awareness is assessed with the Multidimensional Assessment of Interoceptive Awareness (MAIA) [55]. The MAIA is a 32-item self-report questionnaire, measuring eight dimensions covering both the ability to notice bodily sensations and to regulate their influence on behavior. Treatment responsiveness of the MAIA was recently shown in a study on bodily focused contemplative training [56] which found improvements on five of the eight MAIA scales.

#### Mood variability

Trying to measure emotion dysregulation in real life situations, we will assess mood variability with the self-report Mood Zoom, an experience sampling method for real-time mood assessment on a smartphone [57]. Participants are prompted by the phone to rate their current mood on a screen displaying six different moods which have to be scored on 7-point Likert scales. We will prompt participants three times a day, at random time points, over a one-week period per assessment.

### Patient characteristics (and potential predictors of treatment outcome)

Patient characteristics will be assessed during the screening procedure in order to verify in- and exclusion criteria and the formal baseline assessment, to describe the study sample, and to test and control for baseline differences between the study groups. The screening procedure includes the formal assessment of cluster B or C personality disorders, 2) comorbid mental disorders, and 3) cognitive functioning. The formal baseline assessment includes 4) a psychiatric treatment history, 5) socio-demographics, 6) chronic somatic diseases, 7) early life events, 8) alcohol use, 9) current smoking, 10) physical activity and 11) personality traits.

#### Personality disorders

Personality disorders, according to the traditional categorical DSM-5 model, will be assessed with the Structured Clinical Interview for DSM-5 for personality disorders [31]. To minimize patient burden, the interview will be limited to the general diagnostic criteria for a personality disorder and the cluster B or C personality disorder criteria.

#### Mental disorders

Comorbid psychiatric disorders will be assessed with the aid of a DSM-5 checklist. This checklist summarizes all DSM-5 criteria for the following disorders: Major Depressive Disorder, Persistent Depressive Disorder, Manic and Hypomanic Episodes, Bipolar Disorders type I and II, Generalized Anxiety Disorder, Panic Disorder, Agoraphobia, Social Anxiety Disorder, Posttraumatic Stress Disorder, Obsessive Compulsive Disorder, Somatic Symptom Disorder, and Illness Anxiety Disorder. Based on the screening interview with the patient and all available information in the medical records, the psychologist checks which criteria have been present over the past 6 months and which psychiatric disorders are currently present.

#### Cognitive functioning

Global cognitive functioning will be assessed with the Montreal Cognitive Assessment (MoCA). The MoCA is a screening instrument to be administered by trained interviewers (psychologist in this study) for the detection of neurocognitive disorders and assesses a broad range of cognitive domains. We will exclude patients with a sum score below 23 points. A recent meta-analyses showed that a cutoff score of 23/30 shows overall better diagnostic accuracy and a lower false positive for the presence of neurocognitive disorders than the initially recommended score of 26/30 [32].

#### Psychiatric treatment history

Time of first treatment in mental healthcare will be assessed in the structured telephone interview at baseline.

#### Chronic somatic diseases

The presence of chronic somatic diseases is assessed by self-report questions as validated within the Longitudinal Aging Study Amsterdam (LASA) [58, 59]. The questions inquire about the presence of the following chronic diseases: chronic non-specific lung disease, cardiac diseases, atherosclerotic disease of the abdominal aorta or the arteries of the lower limb, diabetes mellitus, cerebrovascular disease, osteoarthritis, rheumatoid arthritis, malignant neoplasms, high blood pressure, stomach ulcers, bowel disorders, liver disease, epilepsy, allergies, thyroid disease, injuries, serious head trauma, and other chronic diseases. The LASA study shows that the accuracy of patients’ self-reports, as compared to general practitioners’ information regarding to the presence or absence of specific chronic diseases, is generally satisfactory [59].

#### Early life events

Childhood trauma will be assessed using a structured inventory previously used in the Mental Health Survey and Incidence Study (NEMESIS) [60]. In this inventory participants are asked whether they have experienced any kind of neglect or abuse before the age of 16. Covered are: emotional neglect, which includes the lack of parental attention or support and interest in one’s problems and experiences; psychological abuse, which includes verbal abuse, punishment without reason, subordination to siblings and being blackmailed; physical abuse, which includes being kicked, hit with or without an object and any other physical harm; and sexual abuse, which is defined as being sexually touched against one’s will, or being forced to touch someone sexually. After an affirmative answer, a question is asked about the frequency of these events, to be recorded as: never, once, sometimes, regularly, often or very often. A childhood abuse index can be constructed by recoding the frequency scores in (0) never, (1) once, sometimes and (2) regularly, often or very often. The scores of each of the four domains of abuse will be summed, resulting in a childhood abuse index which ranges from 0 to 8. Early life-events will be additionally measured and include divorce of parents, placement in children’s home, juvenile prison or foster care, and walking away from home.

#### Lifestyle characteristics

Alcohol use will be assessed with the Alcohol Use Disorder Identification Test (AUDIT) [61], a screening questionnaire for alcohol-related problems in the past year. Current smoking and physical activity will be assessed by two single questions from NEMESIS on current smoking and number of hours per week spent in physical exercise or sport lately, not counting sedentary pursuits such as chess or fishing [60].

#### Personality traits

Pathological personality traits are a second dimension of the DSM-5 alternative dimensional model for personality disorders and can be measured with the 220-item Personality Inventory for DSM-5 (PID-5) [62]. The PID-5 covers 25 pathological personality trait facets, which can be combined to obtain scores for five higher-order domains distinguished. These domains are related to the traditional big five personality traits and to concepts from schema-focused therapy [63]. Most items of the PID-5 are age neutral and thus can be used in older adults [64]. Recently, the PID-5-Short Form (PID-5-SF) has been validated, yielding nearly identical reliability and validity as the long form in scoring the DSM-5 domains and facets [63]. This version will be applied in the present study to minimize patient burden. All items are rated on four-point Likert scales from 0 (very false or often false) to 3 (very true or often true). The combination of pathological personality traits (PID-5-SF) and impaired personality functioning (SIPP-SF) results in the alternative DSM-5 model personality disorder diagnoses.

### Mediators

We will examine whether any improvement on the primary and secondary outcome parameters in patients receiving the experimental schema therapy can be attributed to (i.e. is mediated by) improvements in the therapy specific targets. Mediators are early maladaptive schemes and schema modes, which will be assessed,in the experimental group only, pre-treatment (i.e. in the two initial, individual sessions of treatment) and 3, 6 and 12 months post-baseline, and schemas and modes severity scores, which will be assessed during treatment on a weekly basis.

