**Methods:**

A multicenter RCT with a one-year follow-up comparing group schema-focused therapy enriched with psychomotor therapy (group SFT + PMT) and TAU for adults aged 60 years and older who suffer from either a cluster B and/or C personality disorder. The primary outcome is general psychological distress measured with the 53-item Brief Symptom Inventory. Secondary outcomes are the Schema Mode Inventory (118-item version) and the Young Schema Questionnaire. Cost-effectiveness analysis will be performed from a societal perspective with the EuroQol five dimensions questionnaire and structured cost-interviews.

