### Sample size calculation

The only RCT comparing group SFT with TAU was conducted among younger adults with borderline personality disorder and found a between group Cohen’s *d* effect size (ES) of 2.0 on the Brief Symptom Inventory (BSI-53) [33]. For our power analysis, we tuned down the expected ES to 0.5 (medium effect) for two reasons. First, the ES of 2.0 was partly due to absence of an effect of TAU [34] while meta-analysis of psychotherapy in geriatric psychiatry shows an average pre-post ES of 0.4 for TAU [17]. Second, an open study on group SFT reported a pre-post Cohen’s *d* ES of 0.8 among older adults with mixed cluster B and C personality disorders [21]. Applying a 2-sided alpha of 0.05 and a power of 80% to detect an ES of 0.5, requires 63 patients per arm. Although compensation for dropout is not necessary according to the CONSORT criteria when performing intention to treat analyses (http://www.consort-statement.org/), we aim to include 140 patients in order to compensate for 10% early dropouts during the waiting-list period. Differences in the scores between the intervention and control group on the various outcome measures (BSI-53, EQ-5D-5 L, YSQ and SMI) will be analyzed using linear mixed-models accounting for missing data and relevant confounders.

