#### Early maladaptive schemas

Early maladaptive schemas will be assessed with the self-report Young Schema Questionnaire second version (YSQ-2) [65–68]. The YSQ-2 is the most commonly used measure of early maladaptive schemas [65]. The YSQ-2 consists of 205 items, to be rated along a 6-point Likert scale, which measures the severity of 16 maladaptive schemas. The Dutch YSQ-2 has good reliability and convergent and discriminant validity [69].

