#### Schema modes

Schema modes will be assessed with the Schema Mode Inventory (SMI), a 118-item, self-report questionnaire measuring 16 modes [65]. These modes can be divided into 4 types: healthy modes, parent modes, child modes and coping modes. All items are rated on a 6-point Likert scale. The Dutch SMI has an excellent test-retest reliability and the convergent and divergent validity of the subscales are satisfactory [70].

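### The YSQ and SMI are to be compared between arms as secondary outcomes but are collected only in the SFT arm, so that comparison cannot be estimated, and the one-arm mediator analysis cannot support attribution

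*Protocol article*

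**What the plan says.** The Protocol article gives the YSQ and SMI two roles.

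- **Secondary outcomes compared between arms.** The Methods paragraph of the Abstract states: "Secondary outcomes are the Schema Mode Inventory (118-item version) and the Young Schema Questionnaire". The section Sample size calculation plans linear mixed models for this comparison: "Differences in the scores between the intervention and control group on the various outcome measures (BSI-53, EQ-5D-5 L, YSQ and SMI".
- **Mediators measured in one arm.** The section Mediators states "Mediators are early maladaptive schemes and schema modes" and continues "which will be assessed,in the experimental group only, pre-treatment", with further scores at 3, 6 and 12 months after baseline. The next two sections name the YSQ-2 and the SMI as the instruments, for example "Schema modes will be assessed with the Schema Mode Inventory (SMI), a 118-item, self-report questionnaire measuring 16 modes".

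The rest of the article fits the second role. Table 1 does not list either questionnaire. The sections under Secondary outcome parameters cover psychotropic drug use, Cantril's Ladder, WEMWBS, SIPP-SF, MAIA and Mood Zoom, and leave out YSQ and SMI. The Analyses section has a sentence close to the one in the sample size section, but with a general reference to secondary outcome parameters where that one names YSQ and SMI.

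The mediator question is whether improvement "in patients receiving the experimental schema therapy can be attributed to (i.e. is mediated by) improvements in the therapy specific targets".

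**The concern.** Two statements in the current text cannot both hold. A comparison of arms needs scores from both arms, and the stated collection provides them from one. This is not detail left to an analysis plan, because the article itself makes both statements.

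Three things are at stake.

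- The only secondary outcomes named in the abstract have no between-arm estimate. The methods give a different set, so a reader cannot tell which set was specified in advance. That leaves room for selective reporting.
- The Mediators section asks about mediation of improvement on the primary and the secondary outcomes. If the abstract is right, YSQ and SMI would be asked to mediate themselves.
- The phrase "can be attributed to (i.e. is mediated by) improvements in the therapy specific targets" is causal. A one-arm association between schema change and distress change does not carry that meaning, although the trial randomises a control arm that could help to answer the question.

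**Working it through.** **Step 1. The plan's own figure, for context.** For d = 0.5, two-sided alpha 0.05 and 80% power, n per arm = 2(1.960 + 0.842)² / 0.5² = 62.8, so 63. Allowing for 10% dropout, 2 × 63 / 0.9 = 140. Both agree with the article. The problem is therefore not one of power.

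**Step 2. Can the between-arm contrast be estimated?**

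| Place | SFT arm | TAU arm |
|---|---|---|
| Abstract and Sample size calculation | YSQ, SMI needed | YSQ, SMI needed |
| Mediators | first score in the individual sessions, then 3, 6 and 12 months | none |
| Table 1 (common assessments) | not listed | not listed |

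With no TAU scores, neither the arm effect nor the time-by-arm interaction for YSQ or SMI can be estimated, whatever the number randomised. Mixed models handle scattered missing observations. They cannot supply an arm that is never measured.

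**Step 3. When is the first score taken?** Under Recruitment, baseline measurement precedes randomisation. Under Randomisation, blinding and treatment allocation, patients are then told their allocation. Under the description of group SFT, the YSQ and SMI are given in the two individual sessions that open the therapy. The first score is therefore taken after allocation and is not a trial baseline. This matters if a between-arm analysis is kept. It does not invalidate a within-arm analysis.

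**Step 4. What can the one-arm mediator analysis identify?** Let A be allocation, M the mediator, Y the outcome and U an unmeasured common cause. Take M = aA + uU + e₁ and Y = cA + bM + uU + e₂, with U, e₁ and e₂ independent and of unit variance. The effect of allocation that passes through the mediator is a × b. Within the SFT arm, the slope of Y on M is b + u² / (1 + u²), which does not contain a. The path values below are assumed for illustration and do not come from the protocol; the simulation used 200,000 patients.

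| a | b | c | u | True indirect effect a × b | One-arm slope, formula | One-arm slope, simulated |
|---|---|---|---|---|---|---|
| 0 | 0.5 | 0.5 | 0 | 0 | 0.50 | 0.50 |
| 0.5 | 0.5 | 0.25 | 0 | 0.25 | 0.50 | 0.51 |
| 0.5 | 0 | 0.5 | 0.7 | 0 | 0.49 / 1.49 = 0.33 | 0.33 |

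Rows 1 and 2 have essentially the same slope, although allocation acts through the mediator only in row 2. Row 3 has a clear slope with no mediation.

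The mean change in the mediator does not help. In the SFT arm it equals s + a, where s is the change that would have occurred without SFT. One arm gives the sum only, and the TAU arm is what would separate the two terms.

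**The case against.** The strongest reply is that the article largely settles the role of the YSQ and SMI. The Mediators sections, the secondary outcome sections, Table 1 and Analyses all fit a mediator role. The exceptions are one sentence in the abstract and one analysis sentence placed in the sample size section. This stands as a guide to which text to change. It does not remove the contradiction, since nothing in the article withdraws those two sentences.

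A reader might go on to infer that neither analysis can be done. The documents do not support that. The mediator question is put for patients who receive the experimental therapy, the data for it are collected, and the Background uses the term mediation in the same way for an uncontrolled study of group SFT in older outpatients. The section also says that the question will be examined; it does not yet assert a result. What fails is the causal reading.

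A reader might also divide the two pre-post effects in the sample size section, 0.4 for TAU and 0.8 for group SFT, and conclude that half of the SFT-arm change would be wrongly credited to schemas. That does not follow. The two effects come from different sources (a meta-analysis and a single open study), neither is presented as YSQ or SMI change, and they are not shares of one group's improvement. What a one-arm analysis credits to schemas depends on mediator change and its slope with outcome, and the article gives neither.

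Finally, the trial is not left without secondary outcomes: SIPP-SF, WEMWBS, Cantril's Ladder, MAIA and Mood Zoom are scheduled for both arms. This stands and limits the damage.

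**Conclusion.** The concern holds in two parts. First, the planned between-arm comparison of YSQ and SMI contradicts the one-arm collection and cannot be estimated; the planned control-arm sample for it is zero. This rests on the text alone. Second, the mediator analysis can be run in the SFT arm but gives an association of changes. It cannot separate change produced by the therapy from natural course, regression to the mean or non-specific care, so the attribution wording is unsupported. This rests on the algebra in Step 4. The path values there illustrate the point and do not estimate the size of any bias, and no size can be given from the article.

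The primary outcome, the sample size, the economic evaluation and the secondary outcomes measured in both arms are untouched.

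**What to change.** **Recommended, at the cost of wording only.**

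- Remove YSQ and SMI from the between-arm analysis in Sample size calculation and from the secondary outcomes in the Abstract.
- Name in the Abstract the secondary outcomes that Table 1 and the Secondary outcome parameters sections list.
- Restate the Mediators section as an exploratory, within-arm association between change in schemas or modes and change in outcome, with no claim of attribution.

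**Alternative, if the between-arm comparison or mediation of the treatment effect is wanted.** Collect YSQ and SMI, or SMI alone, in both arms at the pre-randomisation baseline and at the common follow-ups. Keep the 3-month score, in both arms: it is the only planned mid-treatment score on these questionnaires and supports the ordering of mediator before outcome.

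The cost is up to 205 + 118 = 323 items per assessment for TAU patients, or 118 for SMI alone, plus a 3-month contact that Table 1 does not schedule. The inclusion criteria already require every participant to be able to complete these questionnaires, so the option is feasible. The article elsewhere shortens instruments to spare patients, however, so the burden is a real trade-off. Control-arm baselines cannot be recovered for patients already randomised.

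Two-arm data would identify the effect of allocation on the mediator. An indirect effect would still assume no unmeasured common cause of mediator and outcome, and the plan should say so. The weekly severity scores are tied to the therapy sessions and stay within-arm under either option.
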